### Data handling

eDream®, an electronic data capture and clinical data management programme (electronic case report form) will be used to collect and store the data. The database will be hosted and secured on the servers of Diagram and is on-line accessible.

### Statistics

All parameters will be analysed on the intention-to-treat principle. All patients will be analysed in the group they are randomised to. Categorical variables will be summarised by frequency and percentages. Continuous variables will be summarised by mean and standard deviation as well as median and interquartile range.

The primary treatment comparison is telemonitoring group versus control group. Student’s t-tests will be used to examine whether the continuous variables are different between the intervention groups at baseline, at 6 months and at 12 months. When necessary the continuous variables will be transformed to obtain a normal distribution, or a non-parametric test will be used (Wilcoxon rank-sum test). Chi Square tests or Fisher’s exact tests as appropriate will be used to examine whether the categorical variables are different between the intervention groups at baseline, at 6 months and at 12 months.

Time until MACE will be described by Kaplan Meier curves. The Kaplan Meier curves will indicate the occurrence of MACE during 1 year of follow-up. Patients who do not experience an event or are lost to follow-up without an event are censored. Differences in survival distributions between the telemonitoring and control group will be tested using logrank tests.

A two-sided p-value of less than 0.05 will be considered to be statistically significant in all analyses. Analyses will be performed with Statistical Analysis System, SAS, version 9.3 and with the Statistical Package for the Social Sciences (SPSS, IBM) version 22.0.

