**Methods:**

In this single centre randomised controlled trial 120 patients with an absolute indication for cardiac rehabilitation will be randomised in a 1:1 ratio to an intervention group with 6 months of heart rate based telemonitoring guidance or a control group with traditional follow-up after cardiac rehabilitation. The primary endpoint will be VO2_peak_ after 12 months. Secondary endpoints are VO2_peak_ after 6 months, quality of life, physical-, emotional- and social functioning, cardiac structure, traditional risk profile, compliance to the use of the heart rate belt and smartphone, MACE and care-consumption.

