### Sample size

Preliminary calculations suggest that for an expected difference in VO_2peak_ of 3.0 ml/kg/min between the control and intervention group with an estimated standard deviation of 4.8 ml/min/kg, assuming 90 % power and 5 % significance level (α = 0.05), a total of 108 patients is needed to detect a beneficial effect of telemonitoring. These numbers are based on a previous study that shows the effects of 52 weeks of CR with combined supervised and unsupervised exercise sessions [14]. Taking into account a 10 % dropout we plan to randomise 60 patients in each group.

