## Preliminary results

Patient demographics and reasons to refrain from participation are shown in Tables 1 and 2. Preliminary results show that 122 of 299 (40.8 %) consecutive patients meeting the in- and exclusion criteria were willing to participate. They are on average 59 years of age and predominantly male (82,5 %). Main reasons to refrain from participation are the time investment and doubts concerning the added value.

**Table 1 Tab1:** Patient demographics

	Screened	Included
	Number (%)	
Patients screened	299	122
Men	232 (77.7)	101 (82.8)
Women	67 (22.4)	21 (17.2)
Age (mean years)	63.7	59.6

**Table 2 Tab2:** Reasons to refrain from participation

	Number (%)
Too time consuming	64 (36)
Not convinced of added value	40 (23)
Insufficient computer knowledge	25 (14)
Follow-up in a different location	12 (7)
Physical impairment	12 (7)
Too much traveling time	7 (4)
Problems with coping	6 (3)
Holiday > 1 month or abroad during follow up	5 (3)
Heart rate belt is too much stress	3 (2)
Unknown	3 (2)

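### The 12-month primary test is an unadjusted t-test that by default ignores the T0 and T1 VO2peak values: it gives up precision and is exposed to bias if dropout differs by arm

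*Protocol article*

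**What the plan says.** The abstract's Methods paragraph fixes the endpoint: "The primary endpoint will be VO2_peak_ after 12 months". VO2peak at 6 months is a secondary endpoint. Under Design and Cardio pulmonary exercise testing, the exercise test is done in both arms at T0, T1 (26 weeks) and T2 (12 months).

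The Statistics section sets the principle, "All parameters will be analysed on the intention-to-treat principle. All patients will be analysed in the group they are randomised to", and then the method: "t-tests will be used to examine whether the continuous variables are different between the intervention groups". This is done separately for T0, T1 and T2, with transformation or a Wilcoxon rank-sum test where needed. The section mentions no covariate and no model that links the visits. Loss to follow-up is dealt with only for time to MACE, by censoring.

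The Sample size section plans on "an expected difference in VO_2peak_ of 3.0 ml/kg/min between the control and intervention group". The SD is taken as 4.8, the power as 90% and the alpha as 0.05. The section arrives at 108 patients and then allows for loss: "Taking into account a 10 % dropout we plan to randomise 60 patients in each group".

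**The concern.** A two-sample t-test at 12 months has nowhere to put a patient without a 12-month value, and it makes no use of any patient's earlier tests. Two things follow.

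The first is precision. VO2peak measured in the same person a year apart should be correlated, and an analysis that conditions on T0 removes the explained part of the variance. The t-test leaves that gain unused although the data are already scheduled.

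The second is bias. If loss before T2 differs between arms and the patients lost differ in fitness from those who stay, the difference between observed means mixes the treatment effect with selection. The trial is open to patients and care providers, and only one arm has the belt, the smartphone and the coaching calls. Unequal loss is therefore possible, although the article gives no dropout by arm.

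**Working it through.** **1. The plan's own figures.** Inputs from Sample size: difference 3.0, SD 4.8, power 90%, two-sided alpha 0.05 (Statistics).
- The normal-approximation formula gives 54 per arm, 108 in total, as stated. The exact t-test calculation gives 54.8, so 55 per arm.
- 108 / 0.9 = 120, as stated.

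The inflation is correct. It also shows that about 12 of 120 patients are expected to add nothing to the primary comparison.

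**2. Precision.** With 54 observed per arm:
- Unadjusted: SE = 4.8 × √(2/54) = 0.92.
- Conditioning on T0 multiplies this by √(1 − ρ²), where ρ is the T0-T2 correlation. The article gives no ρ, so it is assumed.
- ρ = 0.5: 0.92 × 0.866 = 0.80.
- ρ = 0.7: 0.92 × 0.714 = 0.66.

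Simulated trials with 60 randomised per arm and about 10% lost agree: about 0.91 unadjusted, 0.80 adjusted at ρ = 0.5 and 0.67 at ρ = 0.7. The gain does not come from the missing data. With no dropout and ρ = 0.7 the SE still falls from 0.87 to 0.63.

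**3. Bias by hand.** Let d be the share of an arm lost, and D the amount by which the lost patients' 12-month mean lies below that of the patients observed. Then

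bias of the observed difference = d(tele) × D(tele) − d(control) × D(control).

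The article gives neither D nor the split of loss by arm; both are assumed. Type I error uses SE 0.92.

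| Loss, tele vs control | D = 1.5 | D = 3.0 | D = 4.8 |
|---|---|---|---|
| 10% vs 10% | 0 | 0 | 0 |
| 15% vs 5% | 0.15 | 0.30 | 0.48 |
| 5% vs 15% | −0.15 | −0.30 | −0.48 |

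At 15% versus 5% the two-sided type I error is about 5.3%, 6.2% and 8.1%.

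**4. Bias by simulation.** No treatment effect, 60 per arm, SD 4.8, probability of loss rising as T0 falls (assumed odds ratio 2.0 to 2.7 per SD).
- Loss of 15-18% versus 5-6.5%, ρ = 0.5-0.7: t-test bias about 0.16 to 0.32 ml/kg/min. Against the planned 3.0, 0.16/3.0 = 5% and 0.32/3.0 = 11%.
- The T0-adjusted estimate in the same runs: bias at most about 0.01.
- Equal loss of 10%: both about zero.
- Arms swapped: same size, opposite sign.

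**5. Limit of the adjustment.** The near-zero adjusted bias holds because loss was made to depend on T0 alone. When loss depends on T2 itself, or on the part of T2 that T0 does not explain, the T0-adjusted estimate keeps a bias of roughly 0.15 to 0.34 at ρ = 0.7. In the second of these cases it is biased as much as the t-test.

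**The case against.** The strongest reply is that this is a condensed article. Analysis sets and missing-data rules commonly sit in a full protocol or SAP, and neither is shown. That stands: the lack of a missing-data rule is not raised as an error here. It does not cover the method the article does choose. An imputation rule elsewhere would fill in T2 values, but would not make the stated t-test condition on T0.

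A reader might infer that the plan contradicts its own intention-to-treat statement. The text does not support this. The article explains the principle as analysis by randomised group, and a t-test by randomised group respects that. Nor does the article restrict the test to patients with a 12-month value; that is only what a t-test does by default. Raising 108 to 120 is ordinary sample-size practice, not a decision to exclude anyone.

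A reader might also infer that dropout will favour telemonitoring, because "Too time consuming" leads the reasons for not taking part (64 of 177). Table 2 describes people who declined before randomisation and so are not in the trial. Much of the visit burden is described without distinction between the arms. Telemonitoring ends at T1, so giving up the device is not the same as missing T2. Controls without coaching could equally be the ones who leave. The direction cannot be told from the document.

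Finally, the bias is modest: 0.32 / 0.92 is about a third of one standard error. The proposed model also rests on an assumption about dropout. Both points stand, and the second is why a sensitivity analysis is part of the fix.

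**Conclusion.** The point holds as a weakness in the chosen primary analysis. The precision loss is the firmer part: it needs no assumption about dropout, only a T0-T2 correlation, and at 0.5 to 0.7 the standard error would fall from about 0.91 to 0.80 or 0.67. The bias is conditional. It needs loss that is unequal between arms, or lost patients who differ between arms, together with a link to fitness. Under the assumed 15-18% versus 5-6.5% T0-related loss it is about 0.16 to 0.32 ml/kg/min, 5-11% of the planned effect, and of either sign. The documents do not show that it will occur, and they do not show a breach of intention-to-treat.

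**What to change.** Replace the t-test for VO2peak with one likelihood-based longitudinal model: T0, T1 and T2 as outcomes, a common T0 mean, arm-by-visit effects and unstructured covariance, fitted to all randomised patients with any VO2peak measurement. Take the T2 contrast as primary and the T1 contrast as the 6-month secondary result. The observed-case t-test can be reported as supportive.

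This model removes dropout bias only where loss is explained by the observed VO2peak values. Add one sensitivity analysis that shifts the unobserved T2 values, in either arm, over a stated range and shows where the conclusion would change.

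If a SAP already fixes such a model, cite it and bring the Statistics wording into line. The cost is slightly more analysis work. The three exercise tests are already scheduled in both arms and SAS is already named, so no new visits, patients or software are needed.

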## Methods

### Design

This study is designed as a prospective single centre randomised controlled trial. Patients will be evaluated at baseline (T0), after 26 weeks (T1) and 12 months (T2) after randomisation. Figure 1 provides a flowchart of the study protocol. The study complies with the World Medical Association Declaration of Helsinki on ethics in medical research and is approved by the medical ethics committee of Isala (NL48475.075.14; 14.0334). Clinical Trial Registration: NTR4644.

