### Cardio pulmonary exercise testing

Cardiopulmonary exercise testing will be performed every visit in both groups using individualised cycle ergometer ramp protocols on an electro-magnetically braked cycle ergometer (Lode Corrival, Lode, Groningen, the Netherlands). Twelve-lead ECG is recorded continuously and blood pressure is measured every 3 min. Oxygen consumption and CO2 production will be measured breath-by-breath by ventilatory gas exchange (Metalyzer 3b, Cortex Biophysics GmbH, Leipzig, Germany).

All patients start with 1 min of rest, thereafter 2 min of unloaded cycling, an individualised ramp protocol in order to reach VO2_peak_ between 8 and 12 min, 1 min of complete rest to measure Heart Rate Recovery (HRR) and finally a recovery period of 4 min. Patients will be encouraged to exercise until levelling off of VO2 despite an increase in workload and/or to a respiratory exchange ratio >1.10. Afterwards, patients are asked to quantify their rate of perceived exertion according to the original BORG score. Peak VO2 will be determined as the mean value of the final 30 s of exercise. The following criteria will be used to correlate the CPET at different time points: <100 ml increase VO2 in the last minute, RER (Respiratory Exchange Ratio) ≥ 1.10, BORG ≥ 17, HR (Heart Rate) > 85 % predicted.

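### The primary 12-month VO2peak comparison is planned as an unadjusted t-test, which is valid but leaves unused the baseline VO2peak measured in both groups, giving up precision at no saving

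*Protocol article*

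**What the plan says.** The abstract of the protocol article defines the endpoint: "The primary endpoint will be VO2_peak_ after 12 months". The Statistics section gives one parametric method for all continuous variables: "t-tests will be used to examine whether the continuous variables are different between the intervention groups at baseline", and the sentence goes on to name the 6-month and 12-month visits as well. If normality is doubtful, the variable is transformed "or a non-parametric test will be used (Wilcoxon rank-sum test"), which is also unadjusted. The article mentions no change score, covariate-adjusted model or mixed model.

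The baseline value is available. Under Design, "Patients will be evaluated at baseline (T0), after 26 weeks (T1) and 12 months (T2) after randomisation", and under Cardio pulmonary exercise testing, "Cardiopulmonary exercise testing will be performed every visit in both groups". The Sample size section plans "for an expected difference in VO_2peak_ of 3.0 ml/kg/min between the control and intervention group with an estimated standard deviation of 4.8" ml/min/kg, with 90% power and a 5% significance level. This gives 108 patients, raised to 60 randomised per group for 10% dropout. The section does not say whether 4.8 is the SD of VO2peak itself or of its change.

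**The concern.** Each visit is analysed on its own, so the primary comparison uses raw 12-month values and ignores where each patient started. If T0 and 12-month VO2peak are correlated, part of the 12-month variance is predictable from T0, and the t-test leaves that part in the standard error. The planned baseline test does not help. Under randomisation any baseline difference is due to chance, and testing it adjusts for nothing.

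At stake are the width of the confidence interval and the chance of detecting an effect smaller than the planned 3.0 ml/kg/min. The validity of the result is not at stake.

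**Working it through.** **Inputs from the protocol article.** Difference 3.0 ml/kg/min, SD 4.8, power 90%, 5% level (Sample size); two-sided testing (Statistics); 1:1 allocation (Randomisation); 60 per arm randomised, hence 54 per arm evaluable after 10% dropout.

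**Assumptions.** (a) The correlation r between T0 and 12-month VO2peak is not given; 0.3, 0.5, 0.7 and 0.8 are shown. (b) 4.8 is the SD of VO2peak at both T0 and 12 months.

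**Step 1: reproduce the planned size.** n per arm = 2 × 4.8² × (1.960 + 1.282)² / 3.0² = 53.8, rounded up to 54, so 108 in total; 108 / 0.90 = 120. Both figures agree with the article. An exact noncentral-t calculation gives 89.6% power with 54 per arm and 90.1% with 55. The sample size therefore fits the unadjusted t-test.

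**Step 2: precision after adjustment.** Unadjusted SE = 4.8 × √(2/54) = 0.924. ANCOVA multiplies this by √(1 − r²). The difference detectable with 90% power is (1.960 + 1.282) × SE. Normal approximation throughout:

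| Analysis | SE factor | SE | 95% CI half-width | Detectable difference | Power if true difference is 3.0 |
|---|---|---|---|---|---|
| t-test | 1 | 0.924 | 1.81 | 2.99 | 0.901 |
| ANCOVA, r = 0.3 | 0.95 | 0.881 | 1.73 | 2.86 | 0.926 |
| ANCOVA, r = 0.5 | 0.87 | 0.800 | 1.57 | 2.59 | 0.963 |
| ANCOVA, r = 0.7 | 0.71 | 0.660 | 1.29 | 2.14 | 0.995 |
| ANCOVA, r = 0.8 | 0.60 | 0.554 | 1.09 | 1.80 | >0.999 |

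As an illustration only, suppose the true difference were 2.0 ml/kg/min, a figure that is not in the article. Power would be 0.581 by t-test, and 0.622, 0.705, 0.858 and 0.950 by ANCOVA at the four values of r.

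**Step 3: chance baseline imbalance.** With 60 per arm, the T0 difference between arms has SE 4.8 × √(2/60) = 0.876 ml/kg/min. With equal SDs, the unadjusted 12-month estimate carries r times the observed imbalance. An imbalance of one SE moves it by 0.5 × 0.876 = 0.44 at r = 0.5 and by 0.8 × 0.876 = 0.70 at r = 0.8. Over repeated randomisations this movement is part of the t-test's SE in Step 2, so it is the same loss seen from another side.

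**Step 4: if 4.8 is the SD of change.** With equal SDs, the SD of the value would be 4.8 / √(2(1 − r)), that is 4.1, 4.8, 6.2 and 7.6 at r = 0.3, 0.5, 0.7 and 0.8. Except at r = 0.5, the absolute figures above would change, including the 90% power of the t-test. The SE factor √(1 − r²) would not.

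**The case against.** The strongest reply is that nothing here is an error. Under randomisation the unadjusted t-test is unbiased and holds its 5% level, and the endpoint, test and sample size agree with one another. That stands. A reader might infer from the missing adjustment that the primary result would be biased or the trial underpowered. The documents support neither: at the planned difference and with 4.8 as the SD of the value, power is about 90%.

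A reader might also take a chance T0 imbalance to pass nearly intact into the 12-month result, as a harm on top of lost precision. It does not: it carries over r-fold and is already within the t-test's SE.

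The size of the gain is uncertain, and this stands too. The article gives no r and no within- or between-patient variances, so it cannot be claimed that patients differ much more from one another than from themselves a year later. At r = 0.3 the SE falls by only about 5%.

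The baseline significance tests are a minor matter. No decision is attached to them, and they do not affect the primary result.

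Finally, a separate analysis plan may exist. That would excuse an omission, but here the article names the method and its sample size matches that method. If a later plan already adjusts for baseline, the two need to be reconciled.

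**Conclusion.** The point holds as a worthwhile improvement to a stated method, not as the correction of an invalid one. The planned t-test is sound but less precise than the data allow. For r between 0.3 and 0.8, adjustment for T0 VO2peak would cut the standard error by about 5% to 40% and lower the difference detectable with 90% power from 3.0 to about 2.9 to 1.8 ml/kg/min. If r were near zero, the cost would be one degree of freedom.

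The direction of the gain is secure for any non-trivial r. Its size rests on the assumed r, and the absolute figures also rest on 4.8 being the SD of VO2peak at both T0 and 12 months.

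**What to change.** Amend the primary analysis to an ANCOVA of 12-month VO2peak on randomised arm and T0 VO2peak, and report the adjusted mean difference in ml/kg/min with its 95% CI. Treat the other continuous outcomes measured at T0 in the same way, each with its own baseline value as covariate. Keep the unadjusted t-test as a sensitivity analysis. Present baseline characteristics descriptively, without significance tests. State whether 4.8 is the SD of the value or of change.

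The cost is a short dated amendment, with no new measurements and no more patients. Timing matters. The Preliminary results section already reports 122 patients included, and patients and care providers are not blinded, so the amendment must be fixed and dated before outcome data are examined by arm.

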The main aim of the present study is to determine whether prolongation of a traditional CR programme with heart rate based telemonitoring guidance for a period of 6 months results in better long-term effects on physical and mental outcomes, care consumption and quality of life (QOL). In order to see whether patients are able to sustain their CRF and LTPA levels after the telemonitoring intervention of 6 months, this will be followed by a 6-month period without telemonitoring guidance.

The primary objective of the study is to assess whether the addition of 6 months of heart rate based telemonitoring guidance to the traditional CR programme results in a higher peak oxygen uptake (VO_2peak_) than a regular follow-up 12 months after CR. Secondary outcome parameters are: VO_2peak_ at 6 months, cardiac structure and function, QOL, physical (LTPA level), emotional and social functioning, traditional risk profile, compliance to the use of the smartphone, adherence to the minimum recommendations of LTPA, care consumption (hospital admissions, outpatient clinic visits, general practitioner (GP) visits, cardiovascular interventions and lab testing) and Major Adverse Cardiac Events (MACE).

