### Blood analysis

Venous blood samples will be obtained after an overnight fasting period at baseline, after 6 and 12 months. Total cholesterol, serum triglycerides, high-density lipoprotein, low-density lipoprotein, ApoB, HbA1c and glucose are analysed by the biochemical laboratory using standard procedures for the analyses.

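### One p<0.05 rule covers the primary and some 60 to 66 unadjusted secondary comparisons, so about three chance findings would be called significant if there were no effect anywhere

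*Protocol article*

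**What the plan says.** The abstract names one primary endpoint, which "will be VO2_peak_ after 12 months". The Background section puts the primary objective in the same terms: whether adding telemonitoring "results in a higher peak oxygen uptake (VO_2peak_) than a regular follow-up 12 months after CR". The Sample size section sizes the trial on that endpoint alone.

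The same Background section states a wider main aim, namely whether the extended programme "results in better long-term effects on physical and mental outcomes, care consumption and quality of life (QOL", and the abstract and Discussion repeat it. The secondary outcomes include VO2peak at 6 months and "cardiac structure and function, QOL, physical (LTPA level), emotional and social functioning, traditional risk profile, compliance to the use of the smartphone", followed by adherence to activity recommendations, care consumption and MACE. Individual sections then list the measures. Blood analysis, for example, has seven: "Total cholesterol, serum triglycerides, high-density lipoprotein, low-density lipoprotein, ApoB, HbA1c and glucose are analysed".

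Under Statistics, "Student’s t-tests will be used to examine whether the continuous variables are different between the intervention groups at baseline, at 6 months and at 12" (the last figure is the month of the final visit); categorical variables get chi-square or Fisher tests. For MACE, "Differences in survival distributions between the telemonitoring and control group will be tested using logrank tests". The section ends with the significance rule: "A two-sided p-value of less than 0.05 will be considered to be statistically significant in all analyses". The article gives no number of secondary comparisons.

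**The concern.** The sentence is a stated decision rule. It attaches one label, statistically significant, to the single pre-specified primary test and to every secondary test, at the same threshold and without adjustment. The main aim covers several domains, and the article does not say what a secondary result would mean if VO2peak at 12 months showed no difference.

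The conclusion drawn from the trial is at stake. With many outcomes tested at 5%, a programme with no effect would probably still show a significant difference somewhere. The rule as worded gives a reader no means of separating such a result from confirmatory evidence.

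**Working it through.** **The plan's own figure.** The Sample size section gives a difference of 3.0 and an SD of 4.8 ml/kg/min, 90% power and α = 0.05. Per arm, n = 2(z₀.₉₇₅ + z₀.₉₀)²σ²/δ² = 2 × (1.960 + 1.282)² × 4.8²/3.0² = 2 × 10.51 × 2.56 = 53.8, rounded up to 54. The total is 108, and 108/0.90 = 120. Both stated figures reproduce, and both belong to one endpoint tested once.

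**Step 1: count the secondary comparisons** (after baseline, by visit).

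| Source in the article | Measures | Visits | Tests |
|---|---|---|---|
| VO2peak at 6 months | 1 | 1 | 1 |
| Echocardiography (8 structure, 1 ejection fraction, 10 diastolic) | 19 | 1 (T2) | 19 |
| Questionnaires | 5 | 2 | 10 |
| Blood analysis | 7 | 2 | 14 |
| Weight, systolic and diastolic pressure, waist, hip, lean body mass | 6 | 2 | 12 |
| Care-consumption items | 7 | whole period | 7 |
| MACE (logrank) | 1 | whole period | 1 |
| Adherence to activity recommendations | 1 | 2 | 2 |
| **Total** | | | **66** |

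The count omits baseline tests, separate event types, lung function and the ECG. It also omits smartphone compliance, since only the intervention group is described as receiving the device.

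**Step 2: expected chance findings if every null is true.** The expected number is m × 0.05, and half of that in each direction.
- m = 66: 66 × 0.05 = 3.3 in total; 66 × 0.025 = 1.65 favouring telemonitoring.
- m = 60: 60 × 0.05 = 3.0 in total; 60 × 0.025 = 1.5 favouring telemonitoring.

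Correlation between outcomes does not change these expectations.

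**Step 3: probabilities under independence.** P(at least one) = 1 − (1 − p)^m.
- Either direction: 1 − 0.95⁶⁶ = 0.966; 1 − 0.95⁶⁰ = 0.954.
- Favouring telemonitoring: 1 − 0.975⁶⁶ = 0.812; 1 − 0.975⁶⁰ = 0.781.

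Probabilities of two or more and three or more come from the binomial distribution.

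**Step 4: allow for correlation.** The article gives no correlations, so a common value ρ is assumed. Results are from 400,000 simulated sets of 60 equally correlated normal test statistics.

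| Assumption | Either direction, ≥1 | Either direction, ≥3 | Favourable, ≥1 | Favourable, ≥2 | Favourable, ≥3 |
|---|---|---|---|---|---|
| m = 66, independent | 97% | 65% | 81% | 49% | 23% |
| m = 60, independent | 95% | 58% | 78% | 44% | 19% |
| m = 60, ρ = 0.1 | 94% | 55% | 66% | 38% | 21% |
| m = 60, ρ = 0.3 | 85% | 42% | 48% | 29% | 19% |
| m = 60, ρ = 0.5 | 67% | 31% | 34% | 21% | 16% |

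**Step 5: a narrower count.** Dropping all 6-month tests (1 + 5 + 7 + 6 + 1 = 20) leaves 46. The expected number is 46 × 0.05 = 2.3. Under independence, 1 − 0.95⁴⁶ = 0.91 in either direction and 1 − 0.975⁴⁶ = 0.69 favouring telemonitoring.

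**The case against.** Four points can be made in the plan's defence.

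- **Secondary multiplicity is commonly left to the full protocol or SAP, and neither is shown here.** This stands as far as it goes: the lack of a hierarchy in a condensed article is not a fault. The point here is different. The article does state a rule, for all analyses, and a later document that labelled secondary results exploratory would have to depart from it.
- **The article separates primary from secondary.** This also stands. A reader might infer that the 5% error of the primary test is inflated, or that the plan lets a secondary result establish success. The documents support neither. VO2peak at 12 months is one pre-specified endpoint, and no success rule based on secondary outcomes is written. The broad main aim leaves room for such a claim without prescribing it.
- **The independence figures are too high.** Several measures are tied by construction (E, A and their ratio; S, D and their ratio). Lipids and mood scales are likely to be correlated, and many measures recur at two visits. This is right, and the probabilities should be read as a range down to the correlated rows.
- **The direction of benefit is not defined for every item.** The article gives none for aortic or vena cava diameter, hip circumference or radiology use, for example. The favourable figures therefore assume a direction for each measure, and the count itself depends on how items are grouped. Some counted items, such as hip circumference, are not named individually as secondary outcomes.

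**Conclusion.** The concern holds in a limited form. One unadjusted threshold governs the primary and some 60 to 66 secondary comparisons, under an aim broad enough for a result in any domain to be presented as support. About three chance findings are expected under a global null, about half of them in the programme's favour. At least one in either direction is very likely (67% to 97% across the assumptions shown). At least one favouring telemonitoring has a probability of 34% to 81%.

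A reader might go further and infer that several false benefits are near certain. The figures do not support that: three or more favourable chance findings occur in about 16% to 23% of cases, and about 250 independent tests would be needed for that probability to reach 95%.

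The result rests on a reader's count, on every secondary null being true, and on assumed correlations. It bears on how secondary results are interpreted and leaves the validity of the primary test untouched.

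**What to change.** Reword the closing sentence on significance in the Statistics section along these lines: *The two-sided 5% level supports a confirmatory conclusion for VO2peak at 12 months only. All secondary outcomes are reported as between-group estimates with 95% confidence intervals; their p-values are nominal and labelled exploratory.*

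If the sponsor wants confirmatory status for any secondary outcome, it can pre-specify a short ordered list, tested only after a significant primary result. The list must be fixed before the outcome data are analysed. The article gives no basis for one order over another, so the choice is the sponsor's. The Preliminary results section reports only recruitment and participation data, so nothing in the article shows that outcomes have already been analysed.

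The planned t-tests, chi-square tests and logrank test can stay as nominal tests. Sample size and primary power do not change. The cost is a short rewording and the loss of confirmatory language for secondary outcomes.
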